### Study phases

#### Pre-randomization

Patients who meet the inclusion criteria will be approached by the local investigator or nurse practitioner to explain the Riverleft study and to hand over a patient information form. Candidates will be asked to participate in this study after a one-week reflection period. The nurse practitioner will call back or visit the candidate if the patient is hospitalized, and will obtain a signed ICF. Due to the obligation to give the patient a reflection period of seven days, pacemaker implantations in an acute setting cannot be enrolled in this study.

Eligible candidates, who agreed to participate in the study, will be scheduled for a visit to a cardiologist. During the intake visit, the patient will be asked to complete a health survey questionnaire (SF-36). Further examination includes an electrocardiogram (ECG) and cardiac echocardiography. Left atrial size will be determined in long-axis parasternal view and apical two-chamber view. In addition, left ventricular end systolic and left ventricular end diastolic diameter will be measured and diastolic function will be assessed by computing the ratio of early to late diastolic filling, the E/A ratio.

Medical records will be reviewed to determine the moment of SSS and PAF onset, to document accompanying symptoms during an AF episode and to assess risk factors, prescribed antiarrhythmic drugs and major events which are defined as CVA’s, transient ischemic attacks (TIA) or myocardial infarction. Practical and technological aspects of the selected pacemaker and HM will be explained by the pacemaker technician.

#### Implantation

The atrial lead will be placed in either the RAA (Solia, Biotronik, SE & Co. KG, Berlin, Germany) or dCS (SelectSecure 3830, Medtronic, Inc or Optisense Optim, St. Jude Medical, Inc or Solia, Biotronik, SE & Co. KG, Berlin, Germany). A SelectSecure 3830 will be positioned in the CS by using a steerable sheath (Steerable attain, C304-L6905, Medtronic Inc., Minneapolis, Minnesota, USA). Optimal lead position is determined by continuous monitoring of sensing and threshold and far field R wave (FFRW) values during slow retraction of the sheath. The tip of the steerable sheet will be bent and the lead will be screwed into the wall of the CS. Next, the steerable sheath will be removed completely. Implantation of an Optisense Optim lead (St. Jude Medical, St, Paul, Minnesota, USA), with a short tip-to-ring distance, will be considered in the event of unsatisfactory high levels of FFRW sensing. The investigators haven chosen screw-in leads in order to prevent CS lead displacements and to prevent high levels of atrial thresholds in the CS position as much as possible. A Solia screw-in lead in the CS position will be considered in the event of limited availability of a SelectSecure 3830 or Optisense Optim in the participating centre. A ventricular lead (Solia, Biotronik, SE & Co. KG, Berlin, Germany) is implanted in the RVA position. If this is not possible, the right ventricular outflow tract (RVOT) will be chosen as the alternative pacing site. Lead positioning is confirmed by using fluoroscopy. The implanting specialist will be advised to implant in the RVA or RVOT, in case of possible disparity in implanted numbers of RVA or RVOT between both study arms.

Conventional dual chamber pacemakers (Evia DR-T or Eluna DR-T pacemaker, Biotronik, SE & Co. KG, Berlin, Germany) with HM functionalities will be implanted. The basic rate will be adjusted to 70 beats per minute. Sensor rate and atrioventricular settings will be adjusted according to optimal levels for each individual patient. The closed loop stimulation (CLS) algorithm will be switched on, unless indicated otherwise. Pacemaker settings are encrypted and stored on a USB flash drive (16 gigabyte SanDisk Cruzer Glide USB Flash Drive, SanDisk corporation, Milpitas, California, USA) and imported to a dedicated website.

#### Hospital discharge

The pacemaker technician will give instructions regarding HM and will hand over a CardioMessenger II-S (Biotronik, SE & Co. KG, Berlin, Germany). The CardioMessenger requires only one wall socket and presence of a global system for mobile communications network for the first line of communication. This device will be installed in the bedroom of the participant.

#### Wound inspection

Patients will visit the outpatient clinic one week after pacemaker implantation. The pacemaker pocket will be inspected and in addition, correct functioning of the pacemaker and HM will be evaluated.

#### Run-in time

A three-month run-in time is reserved to allow lead stabilization, optimize pacemaker settings and establish an effective drug regimen. AF episodes registered in the three-month run-in time will not be added to the total number of counted AF episodes. Local investigators are requested to keep pacemaker settings and drug regimen unchanged during the rest of the follow-up period. Unavoidable modifications may be performed but have to be reported.

#### Follow-up

The three year follow-up period will consist of eight outpatient clinical visits. During an outpatient clinical visit, the cardiologist or nurse practitioner will interview the patient and a SF-36 questionnaire will be completed. Drug regimen will be reviewed for changes outside the run-in time. Comparable to the pre-randomization phase, an ECG will be made. Echocardiographic examination will be conducted every year in order to perform the same measurements as described in the pre-randomization phase. The pacemaker technician will assess pacemaker performance, store reports in the pacemaker memory and, if necessary, modifications in the pacemaker settings on encrypted USB flash drive.

Alongside clinical visits, HM will give the investigators the opportunity to receive a report from the implanted pacemaker on a daily basis. The CardioMessenger will automatically receive data from the implanted pacemaker once a day and will send this dataset to the HM website (Biotronik, SE& Co. KG). This report will contain measured values of sensing, threshold, impedance and program settings including CLS.

In addition, HM will report on registered episodes of high atrial rate, number of mode switches and ongoing atrial episodes. The three modules of HM and the connection with the Riverleft website are explained in Figure 2. An Evia DR-T or Eluna DR-T pacemaker (Biotronik, SE & Co. KG) synchronizes with a CardioMessenger, preferably placed on the night table. The CardioMessenger will transmit the acquired data to the HM datacenter. Next, the tailor-made website will receive an email with the acquired data.

**Figure 2 Fig2:**
[figure not shown]
**The three modules of home monitoring and the connection with the Riverleft website.** An Evia DR-T pacemaker (Biotronik, SE & Co. KG) synchronizes with a CardioMessenger, preferably placed on the night table. The minimal distance of 20 cm and the maximum distance of 2 meters are mandatory for correct synchronizing between pacemaker and CardioMessenger. The CardioMessenger will send a report to the home monitoring (HM) center. Finally, an email, with the report attached, will be sent from the HM website to the Riverleft website.

### Adverse events

According to the regulations of the medical ethics committee (MEC), it is compulsory to register all (serious) adverse events. Lead dislocation, pacemaker pocket infection, CVA, TIA and death are considered as (serious) adverse events.

### Dedicated website

We intended a nearly paperless study in order to make the study less vulnerable to errors. For this purpose, a tailor-made website was developed for the Riverleft study. Each participating medical center will have access to a dedicated part of the website. After enrollment and randomization of the participant on the website, obtained data from reviewed medical records and drug regimen, performed interview and ECG, conducted echocardiogram and SF-36 questionnaire will be completed on the website. The website will be completed after each outpatient clinical visit during the follow-up period. The follow-up status of all patients can be viewed instantly.

This website will also receive emails from the HM monitoring website in case of recurrences of AF. Reports on episodes of high atrial rate and number of mode switches will be imported and stored on the website. If necessary, pharmacological therapy will be modified or cardioversions will be scheduled. All adverse events will also be documented on the tailor-made website.

### Safety monitoring

Two committees and one monitor were appointed for patient safety purposes. A data safety monitoring board will review the study progress, make recommendations regarding established protocol and study progress and has the ability to stop the study due to significant benefits or adverse effects in one of the two study arms. This board has three members: an experienced cardiologist, statistician and a researcher. The clinical events committee will study all (serious) adverse events for a causal relationship between event and the Riverleft study. An independent cardiologist will evaluate protocol compliance and study progress by taking random samples in all participating centers.

### Ethics

The study protocol was approved in October 2012 by the MEC (2012-087) in the Erasmus Medical Center, Rotterdam, The Netherlands.

### Statistical analysis

This study is designed to compare recurrences of AF episodes between two treatment groups. Therefore the Fisher’s exact test will be used for this categorical data to assess the difference in AF recurrence. Continuous data regarding duration and total number of AF recurrences will be analyzed by the Student’s t-test. Kaplan-Meier curves will be constructed to compare event-free survival between both groups. Secondary outcomes will be analyzed by a multivariate analysis. A *P* value of 0.05 is considered to be statistically significant.

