### Study population

Patients of 18 years or older, with either intrinsic or extrinsic (antiarrhythmic drug-induced) SSS and at least one PAF episode of 30 seconds or more within six months before enrollment, will be eligible to participate in the study. PAF episodes will be assessed by 24-hour Holter recording, preceding enrollment.

All patients with a clinically estimated life expectancy of five years or less or mental and/or physical inability to accomplish the follow-up period, will be excluded from participation in the Riverleft study. Left ventricular ejection fraction of 40% or less, malignancies and congenital heart defects are also exclusion criteria. Furthermore, chronic obstructive pulmonary disease classified as GOLD 4 and renal disease resulting in a glomerular filtration rate of ≤30 mL/min or creatinine value of ≥250 umol/L will prevent candidates from participation. The local investigator will only enroll eligible subjects after a signed informed consent form (ICF) is obtained.

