### Sample size

A total number of 300 patients is required to detect a difference with a power of 0.8 between both study arms in recurrences of PAF. To maintain statistical power in case of dropout rates as high as 10%, 330 participants will be enrolled.

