### Randomization

Enrolled patients will be added to a tailor-made website, which will automatically randomize participants to either the control group (RAA pacing) or experimental group (dCS pacing). Randomization is stratified for all participating medical centers.

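### Fisher's exact test on categorical AF recurrence does not match the stated primary outcomes (number of recurrences and time between them) and may lose much of the power available

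*Protocol article*

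**What the plan says.** All references are to the protocol article, Methods/Design unless stated.

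- **Statistical analysis.** The section says the study is designed to compare AF recurrences between two groups and draws the test from that: Fisher's "exact test will be used for this categorical data to assess the difference in AF recurrence". It then gives Student's t-test for duration and total number of recurrences, and Kaplan-Meier curves for event-free survival with no test named. On significance, a P "value of 0.05 is considered to be statistically significant".
- **Primary outcomes.** Total number of AF recurrences and time between recurrences. Neither is categorical.
- **Sample size.** The requirement is given in one line: "300 patients is required to detect a difference with a power of 0.8 between both study arms in recurrences of PAF". No rate, effect size, dispersion or test accompanies this. On dropout the section adds: "To maintain statistical power in case of dropout rates as high as 10%, 330 participants will be enrolled".
- **Study population.** Patients have at least one paroxysmal AF episode of 30 seconds or more in the six months before enrolment; "PAF episodes will be assessed by 24-hour Holter recording, preceding enrollment".
- **Follow-up and detection.** Follow-up lasts 36 months. Episodes in the three-month run-in are not counted, which leaves 33 months. The Discussion says symptomatic and asymptomatic episodes are registered automatically, and that a single high-atrial-rate episode triggers a home-monitoring message.

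**The concern.** The test that the text derives from the design question does not analyse either stated primary outcome. Fisher's test needs one category per patient, so it reduces 33 months of device data to whether AF ever came back. A patient with one short episode and a patient with a hundred count the same.

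The design makes this costly. Patients already have paroxysmal AF, detection is automatic, and one episode is enough. If most patients recur in both arms, dCS pacing could remove a large share of episodes and barely move the proportion.

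The yes/no comparison also takes no account of how long each patient was monitored. The article allows for dropout of up to 10%. Its Limitations section withdraws patients with poor atrial sensing or persistent far-field signals, a problem it links to coronary sinus pacing. Monitored time could therefore differ between arms.

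At stake is whether the conclusion about pacing site rests on an insensitive comparison when the trial collects the data for a sensitive one.

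**Working it through.** **The plan's own figure.** The 300 patients for 0.8 power cannot be reproduced, because the article gives no rate, effect or test. The step to 330 is 300 × 1.10 = 330; after 10% dropout, 330 × 0.90 = 297 remain, close to 300.

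**Inputs.** From the article: 300 evaluable patients, significance level 0.05, 33 counted months. Assumed: 1:1 allocation (150 per arm), a two-sided test, and all event rates, dispersions and effects. Fisher power is by full enumeration of the two binomials.

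**1. Is a high recurrence proportion plausible?** The Background and Discussion cite two rates from other settings. Extrapolated at a constant hazard:
- 50% recurrence at 12 months on drugs: 1 − 0.5^(33/12) = 85%.
- 5 recurrences in 12 patients over three months of RAA pacing, read as 5 patients: 1 − (7/12)^11 = 99.7%.

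These make a high proportion plausible; they do not establish it.

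**2. No heterogeneity between patients, 40% reduction.** Treated proportion = 1 − (1 − p)^0.6. Log-rank power = Φ(|ln 0.6| × √D / 2 − 1.96), with D = 150 × (sum of the two proportions).

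| Control | Treated | Fisher | Log-rank |
|---|---|---|---|
| 85% | 68.0% | 93% | 97% |
| 90% | 74.9% | 92% | 98% |
| 95% | 83.4% | 89% | 99% |
| 98% | 90.4% | 76% | 99% |
| 99.7% | 96.9% | 23% | 99% |

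For a 30% reduction, Fisher power is 65% at 85% control recurrence and falls from there (63% at 90%, 55% at 95%), against 79%, 81% and 84% for the log-rank test.

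**3. Patients differ in AF rate (gamma-Poisson), 40% reduction.** With control mean μ over 33 months and dispersion α:
- P(any recurrence) = 1 − (1 + αμ)^(−1/α).
- Rate-ratio power = Φ(|ln 0.6| / SE − 1.96), with SE = √[(1/μ + α + 1/(0.6μ) + α) / 150].

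Worked cell, μ = 50 and α = 2:
- Control: 1 − 101^(−1/2) = 90.0%. Treated: 1 − 61^(−1/2) = 87.2%. Fisher power 9%.
- SE = √[(0.0200 + 2 + 0.0333 + 2) / 150] = 0.1644; 0.5108 / 0.1644 − 1.96 = 1.15; power 87%.

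The t-test column is simulated (4,000 trials per cell, equal follow-up).

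| α | μ | Recur, control v treated | Fisher | Rate ratio | t-test on counts |
|---|---|---|---|---|---|
| 1 | 5 | 83% v 75% | 38% | 98% | 97% |
| 1 | 50 | 98% v 97% | 4% | 99% | 99% |
| 1 | 100 | 99% v 98% | 1% | 99% | 99% |
| 2 | 5 | 70% v 62% | 25% | 84% | 82% |
| 2 | 50 | 90% v 87% | 9% | 87% | 87% |
| 2 | 100 | 93% v 91% | 7% | 88% | 86% |
| 4 | 5 | 53% v 47% | 16% | 57% | 56% |
| 4 | 50 | 73% v 70% | 9% | 60% | 57% |
| 4 | 100 | 78% v 75% | 7% | 60% | 57% |

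Over means 5-100 and dispersions 1-4, Fisher power is 1-38% and rate-ratio power 57-99%.

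**4. What Fisher's test would need.** For 80% power at 150 per arm, 90% recurrence must fall to about 77.5%, or 95% to about 85%.

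**The case against.** The strongest reply is that Fisher's test does not stand alone. The next sentence of the Statistical analysis section plans a t-test on the total number of recurrences, which is a stated primary outcome, and Kaplan-Meier curves follow. Under the same assumptions and equal follow-up, that t-test has almost the power of the rate model (87% v 87% in the worked cell). This stands. A reader might infer that a real reduction would be reported as no difference; the planned count comparison makes that too strong. Nor does the article call Fisher's test primary: its place as the main test is read from its position and from being derived from the design question.

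A reader might also infer that the trial lacks its stated 0.8 power. That cannot be shown. The article ties 0.8 to no effect, rate or test, the missing inputs may sit in the full protocol, and with little heterogeneity Fisher's test exceeds 0.8 for a 40% reduction up to 95% control recurrence. That nearly every patient will recur is likewise inference, since no expected proportion is given. In the high-dispersion rows only 53-78% of controls recur; power is low there because of heterogeneity, and the rate model reaches only 57-60%.

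Finally, the article does not say that an early AF-free dropout counts as a success; handling of incomplete follow-up may be set elsewhere.

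What the reply does not remove: the test drawn from the design question fits neither primary outcome, and Fisher's test was less powerful than the alternative in every case run. The t-test has no stated allowance for monitored time, and the curves have no named test.

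**Conclusion.** The point holds as a mismatch between a stated test and the stated outcomes, with a likely loss of power. For a true 40% reduction and 150 per arm, Fisher power is about 1-38% under gamma-Poisson heterogeneity, where a rate comparison has 57-99%. Without heterogeneity the loss is small at 85-95% control recurrence (89-93% power) and large only very near the ceiling (76% at 98%, 23% at 99.7%).

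These figures rest on assumed rates, dispersion, effect, 1:1 allocation and a two-sided test, and on reading categorical recurrence as yes/no per patient. The documents support saying that the 0.8 power cannot be checked against any named test. They do not support saying that it is false, or that the trial would miss a real effect.

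**What to change.** - **Primary test.** In place of Fisher's test, compare AF amount per monitored time between arms, for example with a negative binomial rate ratio that has an exposure offset and is adjusted for centre (randomisation is stratified by centre).
- **Supportive analysis.** Time to first recurrence from the end of run-in, censored at the end of monitoring, by centre-stratified log-rank test and Cox model.
- **Power.** Restate what 300 patients can detect with the primary test, giving the assumed rate, dispersion and effect.

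The cost is wording in the statistical section and a redone power calculation, with no extra patients or data. The Trial status section says inclusion had not started, so the change could precede any outcome data. The downsides are that the result becomes a rate ratio rather than a simple proportion, and that the restated power may look less favourable if heterogeneity is high (57-60% at dispersion 4 above).

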**Figure 1 Fig1:**
[figure not shown]
**Overview of the Riverleft study design.** Eligible patients will be informed about the study and asked to participate. Signed informed consent will be obtained prior to enrollment. In the next phase, the participant will be randomized between right atrial appendage (RAA) pacing and distal coronary sinus (dCS) pacing. A three-month run-in time will start after implantation. Adjustments to pacemaker settings and prescribed medication can be made without any consequences for the study. After finishing the run-in period, adjustments to pacemaker (PM) settings or prescribed drugs are only allowed if necessary. Electrocardiogram (ECG) will be made at each visit, an echocardiogram et the end of each follow-up year. The study will end for each participant after a 36-month follow-up period.

All participating centers will have an appointed local investigator who will be responsible for appropriate inclusion, implantation and follow-up. Furthermore, all centers will have an independent cardiologist, who patients with questions regarding the Riverleft trial can contact.

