### Primary outcomes

The main objective of this study is to determine the effect of dCS pacing compared to RAA pacing for the prevention of recurrent AF episodes. Total number of AF recurrences and time between recurrences will be assessed and compared between both groups.

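### The t-test on total AF recurrences makes no allowance for monitored time, so more frequent exit in one arm would look like a pacing effect

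*Protocol article*

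**What the plan says.** The Primary outcomes section of the protocol article states: "Total number of AF recurrences and time between recurrences will be assessed and compared between both groups". The Statistical analysis section labels the total as continuous and assigns the method: "Continuous data regarding duration and total number of AF recurrences will be analyzed by the Student’s t-test". The same section plans Fisher's exact test for recurrence and Kaplan-Meier curves for event-free survival. Nowhere does the article mention a rate per monitored time, an offset, a transformation, or a count or recurrent-event model.

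Planned follow-up is the same for everyone: "The study will end for each participant after a 36-month follow-up period". Under Run-in time, episodes in the first three months are not counted, which leaves a 33-month counting window for completers.

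Actual monitored time will vary. The Sample size section allows for loss: "To maintain statistical power in case of dropout rates as high as 10%, 330 participants will be enrolled". Death is listed under Adverse events. The Limitations section says that patients with marginal atrial sensing or persistently high far-field R wave signals leave the study. It names far-field sensing as a potential problem of coronary sinus pacing, which is the experimental arm.

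**The concern.** A patient monitored for 6 of the 33 counted months has had less than a fifth of a completer's opportunity to accumulate episodes. If that patient's total enters the t-test unadjusted, short monitoring reads as successful prevention. Loss that is balanced between arms cancels out. Loss that is commoner in one arm favours that arm, and the sensing rule in Limitations gives a reason to expect more removals with dCS. At stake is a primary comparison that could credit the experimental lead position with a reduction produced by shorter observation.

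There are two lesser worries. Episode counts may be strongly right-skewed, which can cost a comparison of means much of its power. And mean episode duration, which the same sentence assigns to the t-test, exists only in patients who recur, so that comparison is made in subsets formed after randomisation.

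**Working it through.** **Inputs from the protocol article.** Total of 300 at power 0.8, 330 enrolled, dropout up to 10%, significance level 0.05, two arms, counting window 33 months (2.75 years).

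**Assumptions, because the article gives no figure.** 1:1 allocation, two-sided test, 150 per arm, 10 episodes per patient-year, exit times uniform over the 33 months, and partial totals included in the test. Two exit patterns are used. 5% v 15% averages the planned 10%. 5% v 20% averages 12.5%, somewhat above it.

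**Step 1: the plan's own figure.** 300 × 1.10 = 330. Dividing instead, 300 / 0.90 gives 334. The difference is small and is not the point here. The 300 cannot be rebuilt, since the article states only "to detect a difference with a power of 0.8 between both study arms in recurrences of PAF". With 150 per arm it corresponds to a standardised difference of (1.960 + 0.842) × √(2/150) = 0.32. It therefore says nothing about the expected counts or their spread.

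**Step 2: bias in the estimate with no true effect.** A patient who leaves at a uniform time is monitored for half the window on average. With exit fraction d, the expected total is rate × 2.75 × (1 − d/2), so

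ratio of means = (1 − d_dCS/2) / (1 − d_RAA/2).

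- 10% v 10%: 0.950 / 0.950 = 1.00
- 5% v 15%: 0.925 / 0.975 = 0.95
- 5% v 20%: 0.900 / 0.975 = 0.92

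This ratio does not depend on the shape of the count distribution.

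**Step 3: false-positive rate at 5% v 20%.** The shape does matter here. The spurious difference is 27.5 × (0.975 − 0.900) = 2.06 episodes. The SD of a completer's total is √(27.5 + 27.5² × V), where V is the variance of patient rates relative to the squared mean. The standard error is SD × √(2/150), and the test statistic shifts by δ = 2.06 / SE. The normal approximation is P(Z > 1.96 − δ) + P(Z < −1.96 − δ).

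| Patient rates | V | SD | δ | Approximation | Simulation (6,000 trials) |
|---|---|---|---|---|---|
| Gamma | 0.5 | 20.1 | 0.89 | 14.4% | 14.2% |
| Gamma | 1 | 28.0 | 0.64 | 9.8% | 9.4% |
| Gamma | 3 | 47.9 | 0.37 | 6.6% | 6.2% |
| Log-normal, log-SD 1.5 | 8.5 | 80.3 | 0.22 | 5.6% | 4.5% |
| Log-normal, log-SD 2.0 | 53.6 | 201.4 | 0.09 | 5.1% | 3.3% |

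A moderate log-normal tail (log-SD 1.0) gave 8.3%. At 5% v 15% the simulated range was 5.3-9.0% for gamma rates and 3.3-6.0% for log-normal rates. With equal 10% exit it was 3.0-5.2%.

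**Step 4: skew alone.**

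- Gamma rates, equal 10% dropout, 165 per arm: the t-test holds its level, and its power is at most about 5 points below a negative binomial rate model with an offset.
- Gamma rates with V = 2, true rate ratio 0.6: the t-test beats a rank test on the per-patient rate, 85% v 66%.
- Log-normal rates, true rate ratio 0.6: t-test v rank test is 44% v 77% at log-SD 1.5 and 18% v 51% at log-SD 2.0.

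**The case against.** Planned follow-up is identical, so the plan creates no bias by design. A reader might infer that the t-test is biased towards dCS as it stands. The documents do not support that, for three reasons.

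- The bias needs exit after run-in that differs by arm, and no exit rates are given.
- The article does not say that partial totals enter the test. Inflating 300 to 330 also fits an analysis of completers, which would be a selection problem that an offset does not cure.
- The direction is plausible, not established. Sensing is checked at implantation and at each visit, so some removals may come before counting starts. Far-field sensing that goes unnoticed could add false episodes in the dCS arm and push the other way.

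A reader might also infer that inflated false positives and a large loss of power occur together. They barely coexist. At log-SD 1.5-2.0, where the power loss is large, the false-positive rate is not inflated. With gamma rates, where it is inflated, the t-test loses little power.

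Finally, Fisher's test and Kaplan-Meier curves mean that the comparison of AF recurrence does not rest on the t-test alone. That is true, but neither analyses the number of episodes per monitored time. Nor is the method merely left open for an analysis plan: the article names the test for a primary outcome. The core point stands, at reduced size.

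**Conclusion.** The point holds on unadjusted monitored time. The article fixes a t-test on totals for a primary outcome, foresees incomplete follow-up, and contains a removal rule that may act mainly on the experimental arm. Under no true effect and uniform exit times, the apparent reduction is about 5% at 5% v 15% exit and 8% at 5% v 20%, if partial totals are analysed. The false-positive rate is about 5-15% with gamma rates and about 3-5% at log-SD 1.5-2.0, where noise hides the bias in the test but the estimate is still shifted. With equal exit there is no bias.

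Skew is a secondary concern. Its power cost runs from negligible to large, and the documents do not say which applies. This should be fixed, and recruitment had not started according to Trial status. It does not by itself invalidate the trial.

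**What to change.** - **Main count comparison.** Compare post-run-in AF episodes per monitored time, reported as a rate ratio. Use a count model with log monitored days as offset, stratified by centre. Take the p-value from a robust variance or from re-randomisation within centre. A model-based negative binomial p-value should not be relied on: with log-normal rates it rejected a true null in 17-41% of simulated trials.
- **Sensitivity to the tail.** Add a centre-stratified rank test on the per-patient rate. The rate ratio is still a comparison of means, so it does not protect against a very heavy tail.
- **Who is analysed.** State that patients removed for sensing problems stay in the analysis with the monitored time they contributed, and report exit by arm and reason. Add a sensitivity analysis for informative exit, because an offset corrects for length of monitoring but not for exit related to AF risk.
- **Duration.** Also report time in AF per monitored day in all patients, zeros included.

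The cost is analysis wording and a little more programming. Home monitoring is set to transmit daily, so monitored days should be obtainable. The downside is that the result is a rate ratio rather than a difference in means.

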### Secondary outcomes

The relationship between pacing site, reduction of AF episodes, quality of life, heart failure, cerebrovascular accident (CVA), number of cardioversions, frequency and duration of hospital admission and AF progression to persistent AF will be examined.

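### The t-test on raw totals of AF recurrences ignores how much of the 33-month counting window each patient completed, so unequal loss between arms can bias this primary comparison

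*Protocol article*

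**What the plan says.** Under Primary outcomes, the article states: "Total number of AF recurrences and time between recurrences will be assessed and compared between both groups". Statistical analysis then fixes the test: the "total number of AF recurrences will be analyzed by the Student’s t-test". No rate, offset or person-time term is named for the totals. Kaplan-Meier curves are named, but for event-free survival only.

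The counting window follows from two statements. The Figure 1 legend says "The study will end for each participant after a 36-month follow-up period", and Run-in time says "AF episodes registered in the three-month run-in time will not be added to the total number of counted AF episodes". The planned window is therefore the same for everyone, 33 months.

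The article also foresees that some patients will not complete it:
- Sample size: "To maintain statistical power in case of dropout rates as high as 10%, 330 participants will be enrolled".
- Adverse events: death is listed among the events to be registered.
- Limitations: a patient with weak atrial sensing or persistently large far-field R waves is taken out of further participation. Sensing is to be checked at implantation and at each follow-up visit, and far-field sensing is described as a likely difficulty of coronary sinus pacing.

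**The concern.** A total grows with the time over which it is counted. A patient who leaves at month 6 has 3 counted months against 33 for a completer, and one who leaves during the run-in has none. A t-test on totals treats a low count from short observation and a low count from little AF as the same thing.

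This matters between arms only if counted time differs between them or if exit is related to AF. The article itself gives a reason to expect a difference: one of its grounds for ending participation is tied to the experimental lead position. At stake is one of the two quantities named as primary outcomes. This is a stated method, not a detail left open. A later plan that used a rate would replace the announced test rather than complete it.

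**Working it through.** **The plan's own figure.** Enrolment: 300 × 1.10 = 330, as stated. Dividing by the retained share gives 300 / 0.90 = 333.3, rounded up to 334; the gap is small and is not the point here. The 300 itself cannot be reproduced, because no effect size, standard deviation or event rate is given.

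**Inputs from the article.** Window 36 − 3 = 33 months; overall dropout up to 10%; significance level 0.05, taken as two-sided.

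**Assumed inputs (not in the article).** Loss by arm, exit times, mean number of episodes and variation between patients. Exit is unrelated to AF and true AF rates are equal in both arms.

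**Step 1: expected ratio of mean totals if truncated totals are included.** Let f be the mean share of the window counted among lost patients. At equal rates,

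ratio = [1 − loss(dCS) × (1 − f)] / [1 − loss(RAA) × (1 − f)].

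| Loss dCS v RAA (10% overall) | Exits spread evenly (f = 0.5) | All exits before counting starts (f = 0) |
|---|---|---|
| 10% v 10% | 0.95 / 0.95 = 1.00 | 0.90 / 0.90 = 1.00 |
| 12% v 8% | 0.94 / 0.96 = 0.979 | 0.88 / 0.92 = 0.957 |
| 15% v 5% | 0.925 / 0.975 = 0.949 | 0.85 / 0.95 = 0.895 |
| 20% v 0% (extreme) | 0.90 / 1.00 = 0.90 | 0.80 / 1.00 = 0.80 |

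**Step 2: false-positive rate of the t-test on raw totals.** Simulated gamma-Poisson counts with no true effect, 150 per arm, mean 20 over the full window, exits spread evenly, 15% v 5% loss, 4,000 trials per setting:

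| Gamma shape | 0.5 | 1 | 2 | 4 |
|---|---|---|---|---|
| False-positive rate | 5.8% | 6.9% | 9.1% | 12.4% |

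A separate simulation with 165 per arm and one episode per month gave 5.8% to 12.1% for the same losses. Other settings, all averaging 10% loss:
- Equal loss of 10%: 4.8% to 5.1%.
- 12% v 8%: at most about 6.5%.
- 20% v 0%: 9.7% to 39%, as an outer limit.

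The smaller the shape, the more patients differ and the less a small shift in the mean is detected. That is why the rate rises with shape.

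**Step 3: the two alternatives on the same assumptions.**
- Patients with incomplete follow-up dropped: about 5% (5.2% to 5.6%), since exit was assumed unrelated to AF.
- All counted time kept and compared as a rate per person-time: 4.4% to 5.4% in the 165-per-arm simulation and 4.8% to 5.9% in the 150-per-arm one.

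**The case against.** The planned window is the same for every patient and there is no staggered administrative end, so a total over a fixed window is a legitimate target. Bias needs unequal or AF-related exit. That stands, and it makes the point conditional. Kaplan-Meier handles censoring for the first recurrence; that also stands, but it does not cover the totals.

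Four stronger readings are tempting, and the article does not support them:

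- **That patients who leave early will score as having little AF.** Nowhere does the article say that truncated totals enter the test. The statement "A total number of 300 patients is required to detect a difference with a power of 0.8 between both study arms in recurrences of PAF", followed by the inflation to 330, can equally mean 300 evaluable patients after losses. In that case the comparison is among completers and the error figures in Step 2 do not apply.
- **That the error favours dCS pacing.** This holds for exits unrelated to recorded AF. The exclusion ground is a sensing fault, and Limitations says that AF detection depends on sensing. Far-field oversensing could raise the recorded count before exclusion, and weak sensing could lower it. The net direction cannot be read from the article.
- **That the false-positive rate reaches 20%.** At 20% v 5% loss the simulated range is about 8% to 20%. That scenario averages 12.5% loss, above the stated 10%, and its top figure needs the least variable counts tried.
- **That the same fault affects "number of cardioversions, frequency and duration of hospital admission".** These are secondary outcomes, for which Statistical analysis names only a multivariate analysis of unstated form. It may well account for follow-up time.

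**Conclusion.** The point holds in conditional form for the primary AF count. The named test ignores counted time, while the article foresees losses that could differ between arms.

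At the stated 10% overall loss, split 15% v 5% with exits spread evenly, the expected distortion is about 5% of the mean total and the false-positive rate is about 6% to 12%. It is negligible with a mild split or very variable counts, and absent when loss is equal and unrelated to AF. These sizes rest on assumed loss by arm, exit times, mean and dispersion, and on truncated totals being included.

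If incomplete patients are dropped instead, the error rate holds near 5% only while exit is unrelated to AF. Their data are lost, and selection after randomisation is possible otherwise. On either reading a rate analysis is the better choice.

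**What to change.** Replace the t-test on totals for the primary AF count with a comparison of rates, for example a negative binomial model with log counted time as offset. Counted time runs from the end of the run-in to the last monitored day. That day should be obtainable from the daily home-monitoring transmissions described under Follow-up, although the article does not say that it is recorded.

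Include every randomised patient with any counted time. Report by arm the distribution of counted time, the number of patients with none and the reasons for early exit. This reporting is needed because the offset cannot recover patients lost in the run-in and does not fully correct exit related to AF. It also does not repair counts made under faulty sensing.

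The cost is a change of analysis wording and a little extra analysis work. No additional patients or visits are needed.
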